## Abstract

**Introduction:**

Transcranial direct current stimulation (tDCS) may effectively preserve and improve cognitive function in patients with mild cognitive impairment (MCI). Research has shown that Individual brain characteristics can influence the effects of tDCS. Computer three-dimensional brain modeling based on magnetic resonance imaging (MRI) has been suggested as an alternative for determining the most accurate tDCS electrode position based on the patients’ individual brain characteristics to enhance tDCS effects. Therefore, this study aims to determine the feasibility and safety of applying tDCS treatment using optimized and personalized tDCS electrode positions in patients with Alzheimer’s disease (AD)-induced MCI using computer modeling and compare the results with those of a sham group to improve cognitive function.

**Method:**

A prospective active-sham group feasibility study was set to recruit 40 participants, who will be randomized into Optimized-tDCS and Sham-tDCS groups. The parameters for tDCS will be 2 mA (disk electrodes *R* = 1.5 cm) for 30 min during two sets of 15 sessions (2 weeks of resting period in between), using two electrodes in pairs. Using computer modeling, the tDCS electrode positions of each participant will be personalized. Outcome measurements are going to be obtained at three points: baseline, first post-test, and second post-test. The AD assessment scale-cognitive subscale (ADAS-Cog) and the Korean version of Mini-Mental State Examination (K-MMSE), together with other secondary outcomes and safety tests will be used.

**Discussion:**

For the present study, we hypothesize that compared to a sham group, the optimized personalized tDCS application would be effective in improving the cognitive function of patients with AD-induced MCI and the participants would tolerate the tDCS intervention without any significant adverse effects.

**Clinical trial registration**: https://cris.nih.go.kr, identifier [KCT0008918].

## Introduction

1

Alzheimer’s disease (AD) is the most common form of dementia in the elderly (1). It is characterized by progressive memory loss, along with other cognitive impairments (CI) and executive function loss (2). Mild cognitive impairment (MCI) is considered the preclinical stage of AD, with objective CI, functional independence, and a 5–10 percent annual progression rate to dementia (2, 3). Due to the deposition levels of Amyloid-β (Aβ), which have become an indicator to determine the likelihood of developing AD, some individuals have MCI induced by AD (4). Research has found that Aβ might accumulate even before any MCI symptoms appear, meaning that the probability of developing AD existed even before the MCI was diagnosed (4). This means that the neurodegenerative process is already underway, and to date, there is little evidence on the effectiveness of treatments for Alzheimer’s disease and interventions aimed at controlling the disease.

Diverse pharmacological and physical therapies have been studied for MCI; unfortunately, to date, no consistent reports of long-term effectiveness have been published (5). However, increasing evidence suggests that transcranial direct current stimulation (tDCS) may be an effective add-on therapy to improve cognitive function in patients with MCI (2, 6, 7). tDCS is a non-invasive brain stimulation technique that involves placing electrodes on the scalp to apply a weak direct current to the brain cortex with the intent of modulating brain excitability (2). It influences the cognitive and motor functions associated with the stimulated cortical region by modulating the resting membrane potential (8). During the administration of tDCS, depolarization or hyperpolarization of the neuronal membrane of target neurons may be induced according to the polarity of the electrode (anode or cathode), intensity, and time of application (2, 9, 10).

Research has shown that tDCS improves the cognitive state of patients with MCI when applied at an intensity of 2 mA for either 20- or 30 min over periods of 10–20 days (5, 11, 12), showing the potential of tDCS to be used during long-term interventions. According to previous research, tDCS has also demonstrated positive outcomes during long-term interventions for patients with disorders such as depression. In a study involving individuals with major depressive disorder, 15 sessions of anodal tDCS were initially administered, with participants having the option to continue for an additional 15 sessions. The results indicated that those who extended the intervention experienced more lasting benefits than those who completed the intervention after the initial 15 sessions (13). While the past study focused on a different population, it highlights the significance of prolonged tDCS interventions. Hence, assessing the safety and feasibility of tDCS for at least 30 days in patients with MCI is necessary for broader future applications.

Moreover, the effects of tDCS depend not only on the stimulation parameters, but also on distinct individual brain characteristics. A study that included participants with MCI and major neurocognitive disorders applied tDCS at 2 mA for 20 min twice a day for 5 consecutive days but found no significant improvement in cognitive function as assessed through the Mini-Mental State Examination (MMSE) and Alzheimer’s dementia assessment scale–cognitive subscale (ADAS-Cog). According to the authors, the results may have been influenced by various factors, such as a small sample size and the target population, including participants in different stages of neurocognitive impairment (14).

This observation is plausible, given that the progression of MCI disorders affects white matter structural integrity (15). A study found, by using magnetic resonance imaging (MRI), that brain areas with greater preserved white matter structural integrity may be associated with better tDCS outcomes in healthy adults and individuals with CI (16, 17). Furthermore, the structure of the gyri and sulci, amount and distribution of cerebrospinal fluid (CSF), and thickness of the scalp and skull influence the electrical field (E-field) exerted by tDCS on cortical neurons and their subsequent excitability (16, 18). A systematic review published in 2023 recommended that tDCS research in patients with CI should consider individual brain characteristics by developing individually optimized tDCS procedures (19). Also, two previous studies investigating the effects of a combination of tDCS and cognitive training in patients with MCI provided evidence that tDCS affects cognitive changes in the patients, but did not find statistically significant differences with sham tDCS due to a small sample size and did not prove elevated tDCS effect on cognitive training benefits (20, 21). Thus, to determine the feasibility of tDCS as an add-on therapy for MCI induced by AD, brain models based on patients’ individual brain characteristics should be employed for focalized treatment, guided by the resulting E-field outcomes of the brain models.

Brain models require the analysis of individual three-dimensional (3D) T1 MRI to recreate realistic personalized 3D head models. These models are reconstructed from structural MRI and include the main brain tissues (skin, skull, cerebral gray matter and white matter, cerebellum gray and white matter, CSF, and ventricles), specific conductivity assumptions, and electrode properties (22). They enable researchers to determine the E-field using tDCS based on individual brain characteristics, thereby facilitating optimized tDCS applications (23). However, the creation of these models is time consuming and requires the use of multiple software tools to construct an accurate model, which limits their practical use in common clinical settings (23).

Therefore, an accessible software capable of performing brain structure segmentation based on MRI to calculate the E-field induced by tDCS was developed to facilitate the maximal stimulation effect based on individual unique brain characteristics (24). This software has been used previously in research and is expected to facilitate the use of optimized tDCS in clinical settings in the near future (25).

Considering all the above-mentioned studies, the present feasibility randomized double-blind controlled trial study protocol aims to outline the study methods and resources required to determine the feasibility and safety of a treatment for patients with MCI induced by AD with personalized optimized tDCS for the future design of a full-powered trial. The specific aims are to (1) determine the feasibility of optimized tDCS in the treatment of patients with MCI induced by AD for the improvement of cognitive function compared to a sham group, (2) determine the safety of using optimized tDCS in patients with MCI induced by AD, and (3) obtain valid data to sustain the calculation of a sample size for a fully powered trial, should tendencies of efficacy be present.

## Methods and analysis

2

### Trial design

2.1

The trial design is a prospective, multicenter, double-blind, randomized, active/sham group feasibility study. The active control group named the optimized-tDCS group will be compared with the sham-tDCS group to determine the feasibility and safety of optimized tDCS in the treatment of patients with MCI induced by AD. The intervention will be divided into two sets of 15 sessions (five times per week for 3 weeks), with a resting period of a minimum of 2 weeks between sets. In total, the participants will undergo 30 sessions of Active or Sham tDCS (Figure 1).

**Figure 1 fig1:**
[figure not shown]
Study design R, randomization; tDCS, transcranial direct current stimulation; Lt DLPFC, left dorsolateral prefrontal cortex; V, visit.

This study will be conducted and reported according to the Consolidated Standards of Reporting Trials (CONSORT).

### Recruitment and study setting

2.2

The study is expected to take place in the following hospitals: the Catholic University of Korea, Yeouido St. Mary’s Hospital (Seoul, Republic of Korea); the Catholic University of Korea, Seoul St. Mary’s Hospital (Seoul, Republic of Korea); and the Catholic University of Korea, St. Vincent’s Hospital (Suwon, Republic of Korea). Each hospital will screen and recruit volunteers who meet all the inclusion criteria and none of the exclusion criteria below (See Table 1).

**Table 1 tab1:** Schedule of enrollment, interventions, and assessments.

Schedule	Screening	Baseline	tDCS intervention: Set 1		Resting period	tDCS intervention: Set 2	
			3 weeks: 15 sessions	First Post-test		3 weeks: 15 sessions	Second Post-test
Visit	V1	V2	V2–V16	V16	Minimum 2 weeks ±7 days	V17–V31	V31
ENROLLMENT							
Informed consent	V						
Assigning Screening Numbers	V						
Demographic Survey	V						
Medical/surgical history	V						
Evaluation of inclusion/exclusion criteria	V	V					
Vital signs	V		V			V	
Anthropometry and physical examination	V	V	V			V	
Pregnancy test	V						
Laboratory tests	V						V
Prior/Concomitant Medications	V		V			V	
MRI scan	V						V
Randomization		V					
INTERVENTION							
Medical device preparation		V					
tDCS application			V			V	
ASSESSMENTS							
ADAS-Cog	V			V			V
K-MMSE	V			V			V
MoCA-K	V			V			V
HAM-D	V			V			V
S-IADL	V			V			V
Cortical Electric Field Assessment		V					
Adverse events scan			V			V	

tDCS, transcranial direct current stimulation; V, visit; MRI, magnetic resonance imaging; ADAs-Cog, Alzheimer’s disease assessment scale-cognitive subscale; K-MMSE, Korean version of Mini-Mental State Examination; MoCA-K, Korean version of Montreal Cognitive Assessment; HAM-D, Hamilton Depression Rating Scale; S-IADL, Seoul Instrumental Activities of Daily Living.

### Participants

2.3

#### Ethics approval

2.3.1

This protocol was approved by the Korean Ministry of Food and Drug Safety (MFDS) and will be conducted in accordance with the ethical standards of the 1964 Declaration of Helsinki. Additionally, the protocol was approved under the number XC23DSDS0053 by the Integrated Ethics Review Boards of the following universities: Catholic University of Korea, Yeouido St. Mary’s Hospital, Catholic University of Korea, Seoul St. Mary’s Hospital and Catholic University of Korea, St. Vincent’s Hospital.

Participants will sign an informed consent form after receiving a full description of the study’s objectives, benefits, and any potential discomfort they might experience during the intervention.

#### Inclusion criteria

2.3.2

The inclusion criteria will be as follows: (1) individuals aged 60–85 years, both male and female; (2) individuals who meet the criteria based on the diagnostic guidelines provided by the National Institute on Aging and Alzheimer’s Association (NIA-AA) in 2011. Participants will have to meet all core clinical criteria for MCI due to AD and intermediate or high criteria for MCI based on integrated biomarkers. Criteria based on integrated biomarkers, intermediate: (a) Beta-amyloid biomarker positive, neurodegeneration biomarkers no detected, (b) Beta-amyloid biomarker no detected, neurodegeneration biomarker positive; and high: positive Beta-amyloid biomarker and positive neurodegeneration biomarker; (3) individuals with a score of 23 or higher in the Korean version of MMSE (K-MMSE); (4) individuals who meet one of the following criteria: clinical dementia rating global score of 0.5 or lower or Global deterioration scale score of 3 or lower; (5) If an individual is taking acetylcholinesterase inhibitors (ACEI) and N-methyl-D-aspartate (NMDA) receptor inhibitors, only those that have been on the same dosage and usage for at least 3 months from the screening date can be include in the study; (6) individuals taking medications for cognitive function other than ACEI and NMDA receptor inhibitors, as well as medications for chronic conditions such as depression, hypertension, diabetes, hyperlipidemia, and thyroid disorders, the dosage and usage of these medications must remain consistent for at least 1 month from the screening date; (7) individuals with the ability to read and comprehend the informed consent form and participant information sheet, and have sufficient language skills to respond to questionnaires; (8) individuals who voluntarily decide to participate in the clinical trial and provide written consent by signing the informed consent form; (9) individuals available to participate during the entire period of the trial.

#### Exclusion criteria

2.3.3

The exclusion criteria will be as follows: (1) individuals diagnosed with dementia (major neurocognitive disorder) according to the criteria of DSM-5 (Diagnostic and Statistical Manual, fifth edition) or ICD-10 (The International Statistical Classification of Diseases and Related Health Problems); (2) individuals with CI due to the following conditions: Parkinson’s disease, Huntington’s disease, subdural hematoma, normal-pressure hydrocephalus, central nervous system infections (such as human immunodeficiency virus (HIV), syphilis), thyroid disorders, or deficiencies in vitamin B12 or folate; (3) individuals with a history of Axis I psychiatric disorders, including intellectual disability, schizophrenia, alcohol addiction, or bipolar disorder; (4) individuals with a history of seizures within 5 years from the screening date; (5) individuals who meet the following criteria based on computed tomography (CT) or MRI conducted within 1 year from the screening date: acute or subacute hemorrhage, previous large hemorrhage (defined as a diameter exceeding 1 cm on T2 sequence) or previous subdural hemorrhage without documentation indicating that it was not caused by underlying structural or vascular abnormalities, four or more microbleeds (defined as a diameter of 1 cm or less on T2 sequence), any single cortical–subcortical infarct larger than 1.5 cm (or 2 cm on diffusion-weighted imaging for contrast-enhanced MR), surface iron deposition, history of non-stenotic white matter disease defined as less than grade 3 on the age-related white matter change scale (ARWC), any finding that, in the opinion of the investigator, could potentially be a cause of dementia, pose a risk to the participant, or interfere with satisfactory MRI evaluation for safety monitoring purposes*; (6) individuals with brain damage due to trauma, ischemia, hypoxia, or other causes; (7) individuals who have been hospitalized for psychiatric or emotional disorders within 5 years from the screening date; (8) individuals with history of substance abuse within 5 years from the screening date; (9) individuals who have received treatment for alcohol addiction within 5 years from the screening date; (10) individuals whose visual impairment prevents them from reading ordinary writing even with glasses; (11) individuals whose visual hearing impairment makes them difficult to understand conversations even with hearing aids; (12) individuals with difficulty to breath while sitting still; (13) individuals with history of suicide attempts within 6 months from the screening date; (14) individuals with scalp deformities, inflammatory reactions, or other dermatological issues that would hinder EEG and tDCS electrode placement, as determined by a dermatologist; (15) individuals who meet to prohibitions on the use of tDCS medical devices, such as having metal plates inserted in the head, those who have participated in another clinical trial within 30 days from the screening date, those with a history of participation in a different clinical trial for MCI due to AD or prodromal AD within 1 year from the screening date; women of childbearing potential who do not consent to using medically acceptable methods of contraception during the duration of this clinical trial, pregnant or breastfeeding women, and any other clinically significant findings that, in the medical judgment of the principal investigator or responsible personnel, would make the individual inappropriate for this trial.

*In cases without CT or MRI results within 1 year of the screening date, imaging will be conducted to confirm the presence of brain disorders.

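### As written, the white-matter item in exclusion (5) excludes disease below grade 3 and does not catch grade 3, which appears to run opposite to the other imaging findings in that item

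*Protocol article*

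**What the plan says.** Section 2.3.3 of the protocol article opens with "The exclusion criteria will be as follows". Item (5) then covers "individuals who meet the following criteria based on computed tomography (CT) or MRI conducted within 1 year from the screening date", followed by a list of findings. One of them is a "history of non-stenotic white matter disease defined as less than grade 3 on the age-related white matter change scale (ARWC"). The same item also lists:

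- "previous large hemorrhage (defined as a diameter exceeding 1 cm on T2 sequence");
- "four or more microbleeds (defined as a diameter of 1 cm or less on T2 sequence");
- a single cortical-subcortical "infarct larger than 1.5 cm", with a separate limit for diffusion-weighted imaging;
- "any finding that, in the opinion of the investigator, could potentially be a cause of dementia, pose a risk to the participant", or interfere with the MRI evaluation.

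A footnote to the section has imaging done for candidates who have none from the past year, so item (5) reaches every candidate. The Introduction (section 1) reports, as background, that "brain areas with greater preserved white matter structural integrity may be associated with better tDCS outcomes". The white-matter threshold is not repeated, explained or corrected anywhere else in the article.

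**The concern.** An exclusion on a graded finding normally removes people at or beyond some level of severity. Here the phrase below grade 3 has the form of a limit that a participant must satisfy, yet it stands in a list where satisfying the description removes the person. It may be an eligibility limit that was moved into the exclusion list without reversing the comparison, although the article cannot confirm that.

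What is at stake is the population. A hospital that follows the words would turn away people with lower-grade white matter disease and would not be stopped by this item from enrolling someone with grade 3. A hospital that follows the presumed intent would do the reverse. The article names three recruiting hospitals, plans to recruit 40 people, and intends the data to support the sample size of a full trial (section 1, aim 3). White matter also bears on an outcome, because section 2.6.2.4 uses diffusion tensor imaging to assess network connectivity. A rule that is wrong as written could also be carried into the later trial.

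**Working it through.** There is no stated figure to reproduce and no formula applies. The check is a reading of the item in four steps.

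**1. Polarity of the list.** The section heading and the lead-in of item (5) are both positive: whoever meets a listed finding is excluded. No word reverses this for the white-matter entry.

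**2. What the entry does when read literally.**

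| Candidate | Meets the white-matter entry? | Result under this entry |
|---|---|---|
| White matter disease, below grade 3 | Yes | Excluded |
| White matter disease, grade 3 | No | Not excluded |
| No white matter disease | Arguably no, since there is no disease to grade | Not excluded |

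Treating the phrase as a definition of the disease gives the same result, because grade 3 then falls outside the definition.

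**3. Direction compared with the other sized or counted entries in item (5).**

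| Finding | Excludes when |
|---|---|
| Previous large haemorrhage | diameter is above 1 cm |
| Microbleeds | count is four or more |
| Cortical-subcortical infarct | size is above 1.5 cm (2 cm on diffusion-weighted imaging) |
| White matter disease | grade is below 3 |

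The first three exclude on the larger or more numerous side. The fourth excludes on the lower side of its scale.

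**4. Dependence on the scale's direction.** The article gives neither the range nor the direction of the scale.

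- If a higher grade means more change, the entry runs against its neighbours: lower-grade disease excludes and grade 3 passes.
- If a lower grade meant more change, the entry would agree with its neighbours and there would be no inversion.

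The first reading is an assumption. It is supported by the name of the scale, which grades change, and by the direction of the neighbouring entries.

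**Size.** The article gives no distribution of grades among people aged 60 to 85 and no screening counts, so the number affected cannot be derived. For scale only, each enrolled participant on the wrong side of the confirmed rule would be 1/40 = 2.5% of the planned sample, or 1/32 = 3.1% of the stated minimum.

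**The case against.** The strongest reply is that this may be a slip in a condensed English article. The approved protocol is not shown, and nothing indicates that the hospitals screen from the article. Item (11) of the same list has an evident drafting slip that mixes vision and hearing. This stands as a reason to check the approved protocol before concluding that anyone was wrongly screened. It does not make the published threshold right: the item is stated, not omitted, and gives a perverse result if followed, under the assumption about the scale.

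A second reply is that other clauses limit the harm. The investigator-opinion clause in item (5), brain damage from ischaemia or other causes in item (6), and the general judgement clause in item (15) could each keep out a person with grade 3 change. Inclusion criterion (2) also requires the core clinical criteria for MCI due to AD and at least intermediate biomarker evidence. This stands in part. These clauses are discretionary or address something else, and none restores eligibility to a lower-grade candidate whom the entry removes.

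A third reply is that allocation is 1:1 and stratified by hospital (section 2.3.4), so an eligibility error acts before randomisation and on both arms alike. The trial is also a feasibility study without a power calculation (section 2.7). This stands, and it places the harm in who is studied.

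A reader might also infer several stronger claims that the article does not support:

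- That everyone screened with white matter change is misclassified. A hospital applying the intended rule would misclassify nobody.
- That the rule contradicts the Introduction. That sentence is tentative background on structural integrity, mentions no grades and sets no eligibility rule, so the two are in tension only.
- That the rule admits people with the most white matter change, or lets in vascular impairment. The top of the scale is not given, and inclusion criterion (2) and the other exclusions still apply.

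**Conclusion.** The point holds as an error in an operative eligibility threshold. By its words, the entry excludes white matter disease below grade 3 and does not catch grade 3. On the assumption that a higher grade means more change, that is opposite to the three sized or counted findings beside it, and nothing in the article explains or corrects it.

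The consequence is bounded. The number affected is unknown. Whether any hospital applied the literal rule is also unknown. Safeguards elsewhere may have kept out some people with grade 3 change, but not all by rule. The effect is on the composition of the sample, on how far the findings describe the intended MCI population, and on the data handed to a later trial. It is not a bias in the active-sham comparison. The article does not establish the intended cut-off, and this review does not supply one.

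**What to change.** 1. Compare the white-matter entry with the approved protocol and with the rest of item (5). The sponsor should confirm the scale's direction and the intended cut-off.
2. Correct the wording so that the direction is unambiguous, and state which way the scale runs.
3. Ask each of the three hospitals which rule it applied. Section 3 says that recruitment began in August 2023, so a text correction alone cannot change who had already been screened.
4. Check the recorded grade of everyone enrolled, and review the screening records for people turned away under this entry. The latter cannot be recovered by any analysis, so their number should be reported.
5. Report a sensitivity analysis without any participant on the wrong side of the confirmed criterion, beside the analysis of all randomised participants.

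The cost is a short text correction, one query to each of three hospitals, and a check of existing imaging reads for at most the 40 planned participants plus the screening failures. If the approved protocol already has the direction right and the hospitals used it, only the article's wording needs correcting.
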